#### Recruitment process and patient selection criteria

Patients will be recruited according to the following procedure:

1. A procedure common in retrospective research will be used. Former inpatients of the rehabilitation centre with a cerebrovascular ischaemia or a hemorrhagic bleeding will receive an information letter including a prepared answer sheet and a paid envelope. When interested in receiving more information patients may return the envelope with the answer sheet or contact the project leader by telephone or email.

2. Upon receiving answer sheets back in the rehabilitation centre, patients will be sent the patient information sheet to inform them about the planned study.

3. Three to ten days after sending the patient information sheet, patients will be contacted by phone to ask, if they have received the patient letter and if they have any questions they would like to have answered. If the patient is interested, a first appointment will be arranged to provide detailed information about the study procedure and check for study eligibility. This appointment will be arranged at rehabilitation centre, the patient's home or institution.

Additionally, patients will be recruited as leaving inpatients or from the outpatient therapy department of the rehabilitation centre by their treating therapist, through an advertisement at the centre's homepage, and through flyers at several locations of the centre. Interested patients can contact the project leader through their therapist, by phone, email, or mail. Patients will be selected based on the criteria in Table 2.

**Table 2 T2:** Patient inclusion and exclusion criteria

**Inclusion criteria**	**Exclusion criteria**
- Patients after a first-ever ischemic or hemorrhagic stroke - Outpatients or inpatients 3 months after stroke - Ability to stand with or without a cane for at least 30 sec on a normal hard floor - Ability to walk for 20 metres with or without a cane or an orthosis - MMSE with at least 20 points - Age older than 18 years - Signed written informed consent	- Joint replacements (knee, hip, shoulder) - Limiting pain in the upper or lower body (evaluated with an eleven point VAS rating scale) - Limiting range of motion (ROM) in the hip, knee, ankle joint or toes - Body weight more than 90 kilograms - Compromised mental capacity to give written informed consent

#### Study procedure and measurement events

The study procedure and all measurement events are illustrated in Figure 1. After signing informed consent, patients will start with the baseline phase that extends over week 1 and week 2. During this time patients will undergo all clinical measurements twice (BL, T0) at an interval of six to seven days. After the baseline phase all patients will be randomised to one of three study groups: EG1, EG2, or CG. Each group will receive three therapy sessions per week for two weeks, hence six sessions in total. Each session lasts 45 minutes. Based on the main study hypothesis, therapy for EG1 will embed MI training during physiotherapy, while EG2 will receive MI training after the physiotherapy part. For a detailed description please see Section 'Study intervention' on page 14. Baseline measurements will be repeated directly after the therapy session weeks to evaluate short-term effects of the MI intervention (T1), as well as after a follow up period of two weeks (FU). All intervention and assessment sessions will take place at the rehabilitation centre's physiotherapy department.

#### Randomisation and allocation concealment

Patients will be randomly allocated to the study groups (EG1, EG2, CG) to ensure internal validity of results. Group allocation to one of the three study groups will be performed after the second baseline assessment (T0) using a randomisation list. The list has been generated with MATLAB 2007b (Mathworks Inc., USA) by a researcher not involved in the study. The generated list has been sent to the clinic's pharmacist, who is not involved in the study and will have no contact with study patients. The pharmacist will prepare sealed envelopes with the patient allocation based on the randomisation list. Patients will be given the sealed envelope by the treating therapist and they will open the envelop themselves. After opening, envelopes will be stored with the patient's personal documents in a locked cabinet. Only the treating therapist and the research assistant will have access to the documents. The independent examiner will not have access to the documents. Patients will be told not to talk to the examiner about the group allocation or therapy content during the post-intervention assessments. Randomisation will be concealed to the independent examiner until the last follow-up assessment of the patient has been performed.

#### Blinding and study group interaction

Blinding of study personnel in research projects is a main quality criterion of a study [73]. Nevertheless, blinding of therapists in an intervention study who perform experimental treatment in patients is not always feasible, especially if experimental intervention shall be integrated in the therapy. Consequently, hiding the patient's allocation in this setting will not be possible. Therefore, neither therapists nor patients will be blinded in this study. Nevertheless, the assessor of post-intervention and follow-up assessments and the independent statistician who will control statistical analyses will be blinded to patient's group allocation until all assessments have been performed. Interaction of patients with other study participants will be minimised by the following preventive measures:

- The patients will be asked to not speak about their study and therapy content as well as imagery sessions outside their families, and neither to talk to the assessor about the study and session content.

- All examiners will be instructed not to ask patients about their study content.

- All patients are outpatients, coming to the rehabilitation centre for the study intervention only. They do not stay together in one clinic ward.

- Group sessions will be avoided.

#### Motor task and fear of falling

The motor task 'Going down, laying on the floor, and getting up again' is clinically relevant, in particular for older people who have problems with ambulation and balance. This task is an important skill to live independently and maintain activities of daily living (ADL) [46,66]. A fall is defined as an involuntary position alteration that results in laying on the floor or ground. It can cause injuries such as fractures, soft tissue injury or joint dislocations [46,74]. In particular, lacking the ability to get up from the floor is related to fear of falling (FOF) in the elderly [46]. FOF is a psychological construct that helps to estimate an individual's ability to perform ADL without falling [66]. Friedman and colleagues found that FOF can emerge from an experienced fall and it can exist within non-fallers [75]. Patients after stroke have a 2.3 times higher risk of falling than the age-matched normal population [76]. This risk can increase up to 3.4 times if more than one fall already occurred. It is known that a majority of falls happen during day time, indoors as well as outdoors, while walking, and while changing the body position, e.g. from sitting to standing [76]. These findings confirm the relevance of the selected motor task in this intervention study. Hence, it is expected that MI training and physiotherapy sessions will reduce FOF and improve patient's self-confidence in walking.

##### Stages of the motor task

The stages of the motor task are a modified version from the task stages of Bergland and Laake [46]. They proposed a movement sequence with 13 stages that is helpful for training with elderly individuals having FOF. The patient stands facing a mat on the floor. After the instruction 'Get down to the floor mat' the patient moves down to the mat in a standardised procedure to lie straight on the mat with legs extended. After the command 'Stand up' the patient stands up, moving from the laying position on the floor to an upright position by repeating all stages in reverse order. Two stages were modified: the starting position (stride standing) will be included as the first stage because this stride standing is already challenging for patients after stroke. The original stage 5 (to prone kneeling and up) will be left out because only a small portion of patients after stroke are able to bear the trunk weight at the affected hand, arm, and shoulder while maintaining the arm in an extended position.

Motor task stages considered in this study

- Stage 0 - Standing

- Stage 1 - Stride standing

- Stage 2 - To half-kneeling on to a large foam wedge and up

- Stage 3 - To half-kneeling on to a small wedge and up

- Stage 4 - To half-kneeling on a mat and up

- Stage 5 - To high-kneeling on a mat and up

- Stage 6 - To half-sitting on two pillows and up

- Stage 7 - To half-sitting on one pillow and up

- Stage 8 - To half-sitting on a mat and up

- Stage 9 - Side laying on a large wedge and up

- Stage 10 - Side laying on a small wedge and up

- Stage 11 - Side laying on a mat and up

- Stage 12 - Supine laying on a mat and up

The motor task from Bergland and Lake [46] for elderly people contains thirteen stages and the highest level represents the highest level of motor task completion. This classification will be maintained for the modified motor task in this study with stroke patients.

#### Study intervention

##### Therapy session and physiotherapy

All groups receive physiotherapy treatment based on a mixed neuro-physiological and motor learning approach three times a week for two weeks [77]. Patients will be treated by an experienced physiotherapist with a working experience of at least two years in neurological rehabilitation. Each session will include activities while sitting and walking depending on the motor impairment level of the patient. The main content of the sessions will focus on exercises and activities to improve postural control in different starting positions, preferable positions (or surfaces) with small support to bear body weight (e.g. sitting, standing). The motor task 'Going down, laying on the floor, and getting up again' will be practised once during physiotherapy in all study groups. To maintain an equivalent practice level, patients will be asked not to practice the motor task at home during the intervention period.

In the therapy sessions it is not allowed to:

- practice the motor task more than once,

- practice the motor task in a different order,

- practise parts of the motor task on a treatment bench.

##### Embedded motor imagery training (EG1)

The MI intervention will be embedded into physiotherapy of the six therapy sessions which last for 45 minutes each. For EG1 the complete motor task will be divided into its thirteen stages. Each stage will be mentally rehearsed before and after it is once physically practised.

The embedded MI procedure is based on the PETTLEP approach [34] that can be summarised as follows:

- **Physical/Emotion**: Imagination of the motor act where it should be performed, without any prior relaxation exercises, in an active and alert state.

- **Timing**: Duration of the motor task should not exceed the real performance duration.

- **Environment**: Using (personalised) multisensory environmental cues.

- **Task/Learning/Perspective**: Depending on the patient's learning type and its familiarisation with the task, external or internal perspective is chosen.

Patients will be encouraged to rehearse the motor task mentally as often as possible between therapy sessions. They will be asked to keep a diary of their individual mental rehearsals to measure rehearsal frequency.

##### Added motor imagery training (EG2)

After 30 minutes of physiotherapy in each therapy session the participants of EG2 will receive an added MI training. This training will be based on the studies of Page et al. [30,78,79]. Patients will listen to a tape that consists of three parts: part one is a brief relaxation period up to three minutes, afterwards in part two, patients listen to the description of each motor task step that should be imagined, and finally, in part three, patients will have a short period to refocus on the room and the situation (two minutes). Patients will listen to the tape in a separate quiet room in a supine laying position on a treatment bench. As in EG1, participants of EG2 will be encouraged to rehearse the motor task mentally as often as possible between therapy sessions. They will be asked to keep a diary of their individual mental rehearsals.

##### Control group (CG)

Besides receiving physiotherapy during a 30 minutes session, participants in the CG will listen to a tape lasting for 15 minutes. The rationale for the tape is to provide in CG participants with the same therapeutic attention as applied in EG1 and EG2. It is important that the participants do not imagine movements. Therefore, the tape will start with a short relaxation period up to three minutes. Afterwards patients will listen to information about stroke: its cause, its consequences for different body functions and its recovery phase, therapy options, prevention of potential complications, self-help groups and their offers. This control protocol has been used in other MI studies without negative effect reported by authors [30,80]. All tapes will have an encouraging character and patients will be asked how they liked the information on the tape. Patients will listen to the tape in a separate quiet room in a supine laying position on a treatment bench.

The CG is a very vital aspect of this pilot study to show a treatment effect of both experimental groups versus a CG [81-83]. Since the PETTLEP approach has been investigated in athletes, its efficacy in a stroke population is not known. Therefore, a CG helps to determine the benefit of embedded MI following the PETTLEP approach in a stroke population. Furthermore, if no difference between both experimental groups can be detected a comparison with the CG will show the overall effect of the MI intervention. Without this option no conclusion could be drawn from the experimental intervention and the scientific value of the investigation would be diminished.

Embedded MI (as in EG1) is the novel MI approach investigated in this study. Added MI (as in EG2) is the current MI therapy standard against EG1 will be benchmarked. The investigated methodologies result in different therapist contact times for all study groups. To nevertheless compare all groups in this study, a methodology was implemented to minimise the effect of different therapist contact times. Our approach is to embed the tape listening (EG2, CG) into times of patient-therapist contact and cue the patient involvement. In particular, the following measures have been taken:

- The tape used in EG2 and the CG has been recorded with the research therapist guiding the patient. Hence patients hear the same voice from the tape as they are used in the physiotherapy training.

- While listening to the instructions from the tape, patients in EG2 will be asked to imagine the complete motor task and to report the number of motor task imaginations to the research therapist afterwards. That request has been included to remain concentrated and attentive during the added MI session.

- Before and after listening to the tape (EG2, CG), the research therapist will be present in the room, to help patients in sitting up and put on/off cloths. The therapist will ask patients how they liked the tape content.

#### Statistical analyses

All necessary statistical analyses will be performed with the Statistical Package for the Social Sciences (SPSS) version 16. The significance level will be set at p ≤ 0.05. For all outcome measures the final analysis method will be determined after data collection tests of normal distribution and homogeneity of variances. Before data analyses collected patient data will be anonymised.

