##### Primary outcome measure

The primary study outcome has been defined as changes in time needed to perform the motor task due to the study intervention. This primary outcome will be assessed by the difference between measurement points T0 and T1. For performance and validity reasons all assessment sessions will be videotaped. Time needed to perform the task in seconds will be derived from the video recordings.

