##### Group comparison

Group equality will be determined at baseline regarding all descriptive variables: age, gender, disease, affected brain hemisphere, time since stroke onset, cognitive function, handedness, rehabilitation history, patient's sports history, and patient's history of falls since stroke onset (over the last six to twelve months). Parametric and nonparametric tests will be used depending on statistical data level and data distribution. Furthermore, inter-group comparisons between BL and T0, T0 and T1, as well as T1 and FU will be calculated to analyse changes among all three groups over time. Additionally, intra-group comparisons for each measurement event (pre- and post-intervention; T0 vs. T1 vs. FU) will be calculated for all three groups; means, standard deviations and confidence intervals, will be given where feasible. An intention to treat analysis will be performed for drop outs. Missing values will be replaced by the average trend of all participants of the respective group.

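### The primary test is left open until after data collection, and nothing keeps the statistician blinded while it is chosen

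*Protocol article*

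**What the plan says.** Three places in the protocol article bear on this.

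- **Statistical analyses** sets the timing of the choice: "For all outcome measures the final analysis method will be determined after data collection tests of normal distribution and homogeneity of variances". The same paragraph fixes the criterion: "The significance level will be set at p ≤ 0.05".
- **Primary outcome measure** defines the variable: "This primary outcome will be assessed by the difference between measurement points T0 and T1", in seconds, read from video. The research question makes EG1 versus EG2 the contrast of interest.
- **Blinding and study group interaction** says that "the independent statistician who will control statistical analyses will be blinded to patient's group allocation until all assessments have been performed".

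**Group comparison** adds that "inter-group comparisons between BL and T0, T0 and T1, as well as T1 and FU will be calculated" and, earlier in the same paragraph, that "Parametric and nonparametric tests will be used depending on statistical data level and data distribution". The second sentence directly follows the one on baseline comparability, so it is only weak evidence about the primary outcome.

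The article names no primary test or model, no distribution test, no cut-off and no fallback. It does not say who makes the choice. It says that data will be anonymised before analysis, but not that group codes will be masked.

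**The concern.** Leaving test details to a separate analysis plan would be ordinary and no fault. Here the article goes further and sets the moment of decision after the data are in. An analysis plan that named the method earlier would contradict this sentence, and one that obeyed it would still choose late.

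The only blinding promised to the statistician runs to the end of the assessments, which is also when the data needed for the choice become complete. If allocation is released at that point, whoever picks the method can see what each candidate would show. The nominal 5% level would then no longer describe the procedure used. The summary of effect would also be open, since a t-test compares mean seconds and a rank test compares the ordering of changes.

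The article's abstract says the results will decide whether embedded imagery is superior to added imagery, and no sample size is planned. A primary analysis fixed in advance is therefore one of the few safeguards left.

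**Working it through.** **1. The timing, from the text.**

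- Earliest point at which the method is fixed: after data collection (Statistical analyses).
- Latest point to which the statistician's blinding is guaranteed: completion of all assessments (Blinding and study group interaction).
- Overlap in which the choice is guaranteed to be blinded: none.

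The text neither says that allocation is released before the choice nor prevents it.

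**2. The size, by simulation.** The article gives alpha = 0.05 and no sample size, standard deviation, power or effect, so there is no figure of its own to reproduce. Everything else here is an assumption: two arms (EG1, EG2), no true difference, two-sided 0.05, log-normal task times, correlation 0.7 between T0 and T1 on the log scale. The outcome is d = T1 − T0 in seconds. The mechanical rule is: Shapiro-Wilk in each arm; if either rejects, Mann-Whitney; otherwise Levene, then t or Welch.

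False-positive rate, log-SD 0.6, 6,000 trials per cell:

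| Procedure | 15 per arm | 20 per arm |
|---|---|---|
| Fixed t-test on d | 5.1% | 4.7% |
| Mechanical rule | 5.3% | 4.8% |
| Smallest p of t, Welch, Mann-Whitney | 6.6% | 6.1% |
| The same plus ANCOVA on T0, in seconds | 8.3% | 7.7% |
| The same plus t-test on log change | 9.4% | 8.8% |

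The Monte Carlo standard error near 5% is √(0.05 × 0.95 / 6,000) = 0.28 points.

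A second set with log-SD 0.5 and 4,000 trials (standard error √(0.05 × 0.95 / 4,000) = 0.34 points) gave, at 15 and 20 per arm:

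- mechanical rule: 5.0% and 5.7%
- smallest p of the three tests: 5.8% and 6.5%
- smallest p of six analyses (the three tests, percent change, ANCOVA in seconds, ANCOVA in log seconds): 9.3% and 10.6%, and 9.2% and 10.0% on repetition

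**3. Sensitivity.** Over 10 to 30 per arm, with normal or skewed times, the fixed t-test stays at 4.5 to 5.1%, the rule at 4.8 to 5.3%, the three-test menu at 5.5 to 6.6%, and the menu with ANCOVA and log change at 7.6 to 9.4%.

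**4. Reading the figures.** The excess over 5% is 5.8 − 5 = 0.8 to 6.6 − 5 = 1.6 points for the three-test menu. It is 8.8 − 5 = 3.8 to 10.6 − 5 = 5.6 points for the wide menus. These are worst cases within each menu, because they assume the smallest p-value is always taken.

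**5. Does the choice matter, and do the pre-tests settle it?** With log-SD 0.5 and 15 per arm, both arms pass Shapiro-Wilk in 64% of null trials although the times are log-normal. With an assumed log effect of 0.35, t and Mann-Whitney disagree on significance in 12% of trials.

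**The case against.** The strongest reply is that the declared triggers are distribution checks and not p-values. Applied mechanically, such a rule holds type I error near 5%. That stands: the harm needs a departure from the stated trigger, which the text leaves room for because it names neither tests nor cut-offs.

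Three stronger readings are tempting, and the documents do not support them.

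- **The choice is made with group results visible.** No sentence says so. The blinding section gives a minimum duration, and the statistician might remain blinded for longer. Only the absence of protection is established.
- **The error rate is about 10%.** That figure needs percent change, covariate adjustment and a log scale, none of which the article mentions. It defines the outcome as a difference in seconds and otherwise speaks only of parametric and nonparametric tests, for which the worst case is about 6 to 7%.
- **Late selection costs power.** Under log-normal times with log-SD 0.5, 15 per arm and an assumed log effect of 0.35, the rule-selected test has 52% power and a log-time ANCOVA with both baselines 78%. But a fixed t-test has 51% and a fixed Mann-Whitney 52%. The gap reflects baseline adjustment and log scale under the assumed model, not the timing of the choice.

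It is also fair to say that this is a condensed article on a pilot study, and that contrast, variable, unit and interval are stated. What remains open is the test and, with it, the summary measure. Pilot status does not remove the point, since a significance criterion and a superiority claim are both set out.

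**Conclusion.** The concern holds as a badly fixed rule. The method for every outcome, including the primary, is expressly deferred until the data are collected, and no provision keeps that decision blinded. That the choice could be made with allocation known is an inference from two sections, not a declared plan.

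The likely inflation is modest: none to speak of if a rule is followed mechanically, and about 1 to 2 points if the choice is free among t, Welch and Mann-Whitney. It reaches about 4 to 5 points only if adjustment and scale are treated as open too. All of these rest on assumed arm sizes of 15 to 20, log-normal times and a correlation of 0.7. The defect is worth correcting because the correction is nearly free, not because the stated procedure is shown to fail.

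**What to change.** In **Statistical analyses**, replace the sentence that defers the method with one named primary analysis, for example:

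*The primary analysis compares EG1 with EG2 by ANCOVA of T1 task time on T0 task time, in log seconds. A rank-based comparison is reported as a sensitivity analysis whatever the distribution of the data.*

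The scale must be fixed now, whichever is chosen. If seconds are kept, ANCOVA of T1 on T0 gives the same group effect as ANCOVA of the change on T0, so it stays with the defined outcome.

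In **Blinding and study group interaction**, extend the statistician's blinding: arms are coded A/B/C until the method and the database are locked and the primary analysis has been run.

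The cost is a few sentences, with no extra patients or assessments. There are two downsides. The team gives up the freedom to switch method later, which the sensitivity analysis partly covers. On the log scale the effect is a ratio of times and not a difference in seconds, so the definition of the primary outcome would have to be worded to match.
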